#### Step two

In this step a sub-sample of the survey respondents who self-identify as taking five or more medicines (including complementary, alternative and/or OTC medicines) will be invited to participate in a 15-min telephone interview about any unwanted or ‘when required’ medicines they have at home. The structured interviews aim to build on survey findings by exploring the quantity and nature of unwanted or ‘when required’ medicines that may require disposal, and to explore participants’ perceptions related to disposal practices.

##### Participants

We propose to interview around 5% of the survey sample (i.e. 215 participants). Participants will self-select into the interview sample when they indicate they take five or more medicines in a screening question at the conclusion of the main survey. They will be asked to provide their telephone contact details for follow-up by a member of the research team. The research panel company will provide the researchers with a separate Microsoft Office Excel® spreadsheet containing contact information only (i.e. not including any survey response data). Attempts will be made to contact respondents sequentially at a range of times (including daytime, evenings and weekends), however purposive screening may need to be used to achieve a national representative sub-sample based on gender, age and geographical location from the 2011 census data [25].

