##### Participants

An experienced research panel company (Research Now®) have been contracted to undertake the data collection with an existing panel of individuals who represent the Australian adult population. Research Now® will invite participation to achieve a national representative sample based on gender, age and geographical location from the most recent census (2011) data (Table 3) [25].

**Table 3 Tab3:** General population survey sample characteristics

	Australian representative sample [25] %	Survey sample targets for *N* = 4302 n
Gender		
Female	51	2193
Male	49	2107
Age range (years)		
18–24	12	516
25–34	18	774
35–44	19	817
45–54	18	774
55–64	15	645
65–99	18	774
State or territory		
Australian Capital Territory	2	86
New South Wales	32	1376
Northern Territory	1	43
Queensland	20	860
South Australia	7	301
Tasmania	2	86
Victoria	25	1075
Western Australia	10	430

The most recent Australian Bureau of Statistics survey about waste disposal practices (conducted in March 2012) included data from 12,870 households. This survey used a multi-stage area sampling method [21]. A sample size of 4300 is proposed for our general population survey to enable comparison with the Australian Bureau of Statistics survey results.

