Working with Research Now®, a user-friendly survey which could be completed on-line, or using mobile devices such as smartphones, was developed. For all questions with six or more multiple-choice options the option list is randomised. The online survey has been soft-launched with 48 panel members to test the response algorithms. For the survey proper, Research Now® will invite participation from its panel members to ensure good sample representation and adjust when necessary to ensure targets for under-represented groups (e.g. younger people) are met for the survey sample (*n* = 4300). Survey respondents will be provided with compensation for their time in accordance with terms of their enagagement with Research Now®.

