##### Data analysis

Data related to medicines in the home will be entered into a purpose-built Microsoft Access® database and descriptive analyses conducted. The interviews will be transcribed verbatim by an external transcribing company known to the research team who will sign a confidentiality agreement as part of their contract. Transcriptions will be quality checked and thematic analysis conducted of the qualitative responses to open-ended questions, by two pharmacist researchers with experience in qualitative research using NVivo 11®. This will involve coding and categorising units of data until themes emerge. Transcripts will be constantly compared and contrasted so that higher-order themes are identified (i.e. constant comparison method [28]). The target number of interview participants is 215, however, data collection will cease once no new information is offered i.e. data saturation has been reached.

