## Discussion

### Limitations

In Stage one there are both strengths and limitations with using the Australian Medicines Terminology (AMT) as the basis of the bin audit database. Using this terminology ensures consistency in the medicines terms used; however, as PBS data has not yet been fully reconciled with these terms, the matching of PBS data is incomplete. Manual matching will need to be undertaken for the subset of medicines for which matching could not be automated. Further, a proportion of items will have to be manually entered, with a potential for error, and making data cleaning and analysis of this subset more difficult and time consuming. The bin audit data collection process will involve around 15 pairs of data collectors and three additional research assistants: one at each site to work with the Data Collection Manager. This is a practical solution to manage the size and geographical needs of the audit, however it introduces challenges for standardisation. Consequently, we have introduced a number of strategies to minimise this issue which include: standard operating procedures; data collection protocols and training; real-time data entry directly into a database with limited free-text options; oversight and scrutiny by the Data Collection Manager at all sites; and quality checking of medicines audit processes and data entry for all data collectors.

In Stage two the general population survey will be delivered by an experienced panel research company and participation is restricted to people registered with the company and with internet access. Recruitment via a research company may introduce a degree of selection bias. Similarly, survey participants will self-select into the interview process from the survey, on the basis of taking five or more medicines, and not all potential participants will be contactable. Strategies to minimise selection bias include conducting interviews at a range of times including evenings and weekends and screening participants purposively. It may not be possible for participants in multiple occupancy households to provide information for the entire household, potentially resulting in under-reporting of the overall volume of unwanted medicines in that particular home.

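### Sequential calling of interview volunteers, with an early stop, may let list position influence who is interviewed; a random call order within batches would remove that order effect

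*Protocol article*

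**What the plan says.** All places are in the protocol article.

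- **Call order** (Stage two, Step two, Participants): "Attempts will be made to contact respondents sequentially at a range of times". The key by which the list is ordered is not given.
- **Correction for imbalance** (same sentence, continuing): "however purposive screening may need to be used to achieve a national representative sub-sample based on gender, age and geographical location". The Limitations section repeats this without the condition: "Strategies to minimise selection bias include conducting interviews at a range of times including evenings and weekends and screening participants purposively".
- **When interviewing stops** (Step two, Data analysis): "The target number of interview participants is 215", but "data collection will cease once no new information is offered i.e. data saturation has been reached".
- **Source sample** (Step one, Participants): "A sample size of 4300 is proposed for our general population survey".
- **Survey fieldwork** (Step one, Survey and data collection): the panel company will invite members and "adjust when necessary to ensure targets for under-represented groups (e.g. younger people) are met for the survey sample".
- **What callers know beforehand** (Step two, Participants): the panel company's file gives contact details and no survey answers. Under Interview guide and data collection, demographic questions come at the end of the interview.

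**The concern.** A sequential call order combined with a stopping point means that people far down the list may never be called. That is harmless if list order is unrelated to who the people are. It may not be harmless here, because survey invitations are adjusted to fill groups that fall short of target. A shortfall has to be seen before it can be corrected, so topped-up groups may tend to complete the survey later. If the contact sheet is in completion order, stopping part-way would thin them out.

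The Study design overview makes the volume of unwanted or expired medicines in these households a quantitative objective, and the plan wants a nationally representative sub-sample. Who is called therefore bears on a descriptive estimate as well as on the themes. A stop at saturation would shorten the called part of the list and make any order effect more likely to appear. Calling at varied times helps with who answers the phone; it does nothing for people whose place on the list is never reached.

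**Working it through.** **The plan's own figure.** 5% of 4300 = 0.05 × 4300 = 215, as stated. Table 3's header gives 4302, and 0.05 × 4302 = 215.1, which rounds to the same number.

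**Inputs the documents do not give (assumed, with ranges).**
- V, number of volunteers: 215 to 860, that is 5% to 20% of 4300.
- c, proportion of those called who are interviewed: 50%, 70% or 100%.
- g, a group's share of the volunteers: 12%. This is the 18–24 share in Table 3, borrowed for illustration; the true share among people taking five or more medicines is unknown.
- L, proportion of that group's volunteers lying in the last quarter of the list: 25% (no late concentration), 50% or 75%.

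**Step 1: how much of the list is called.** People called = min(V, 215/c), where 215/0.5 = 430, 215/0.7 = 307 and 215/1 = 215. The fraction called is f = people called / V.

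| V | c = 50% | c = 70% | c = 100% |
|---|---|---|---|
| 215 | all | all | all |
| 300 | all | all | 72% |
| 430 | all | 71% | 50% |
| 645 | 67% | 48% | 33% |
| 860 | 50% | 36% | 25% |

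In 6 of the 15 combinations the whole list is called and order cannot matter. In the other 9, between 25% and 72% is called.

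**Step 2: the group's share among those called.** Assume the group is spread evenly within the first three-quarters of the list. When f is at most 75%, its share among those called in list order is g × (1 − L)/0.75:
- L = 25%: 12% × 0.75/0.75 = 12%
- L = 50%: 12% × 0.50/0.75 = 8%
- L = 75%: 12% × 0.25/0.75 = 4%

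With random order the expected share is 12% for every L. All of this is before any purposive screening.

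**Step 3: sensitivity to non-contact.** Suppose 15% to 25% of respondents take five or more medicines and half of them volunteer (assumptions). The list then holds 4300 × 0.15 × 0.5 = 322 to 4300 × 0.25 × 0.5 = 537 people. If everyone called were interviewed, 215/322 = 67% or 215/537 = 40% of the list would be called. If only half were, 430 people would be needed: the list of 322 is exhausted, and 430/537 = 80% of the longer one is called. The Limitations section expects some non-contact, so 40% to 67% is the full-response extreme.

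**Step 4: early stop.** Take V = 430 and c = 50%, where 215 interviews use the whole list. If saturation were declared at 150 interviews (assumed), 150/0.5 = 300 people would have been called, or 300/430 = 70% of the list, and the 8% and 4% figures of Step 2 would apply.

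**The case against.** The strongest objection is that the plan already has a corrective. The sentence on sequential contact goes straight on to purposive screening by gender, age and location, the same three variables as the survey quotas, and the Limitations section lists that screening among its strategies. A reader might infer from the word sequentially that early survey completers will fill the interview sample. The documents do not support that. They do not say that the list is in completion order, that topped-up groups complete late, or that there will be more volunteers than calls. The word could also just mean working through contacts one after another.

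Two further objections carry weight. A random order reproduces the volunteer pool, which is itself self-selected, so it does not deliver a census profile. Step two is descriptive and thematic, its selection bias is already acknowledged, and a separate interview protocol that is not shown may hold more calling detail.

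Most of this stands, and it limits the point to a conditional one. It does not remove it. The article itself states the call order, so this is not a detail merely left to a fuller document. Screening is only a possibility where the rule is set. The article does not show how callers would know age or gender before a call, given a contact-only file and demographics asked last. Even if applied fully, screening balances three variables and leaves other differences between early and late completers untouched.

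**Conclusion.** The point holds as a minor, conditional weakness in a design choice. Position on the list may influence who is interviewed if two unstated conditions are met: the list follows completion order, and it holds more volunteers than need to be called. A group concentrated late in the list may then be under-represented, in the illustration by a fall from 12% to 8% or 4% before any screening. The effect is nil if the whole list must be called or if no group is concentrated late. These figures rest on assumed pool size, interview success rate and late concentration; they show how the mechanism scales and do not predict the result.

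A reader might also infer that random ordering would make the interview sample representative. It would not: it removes the order effect only, and self-selection into the interview and failure to reach people remain.

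**What to change.** In Step two, Participants, replace sequential contact with a computer-generated random call order within each batch of volunteers received from the panel company. Keep the planned purposive screening alongside it: where gender, age and location are known before calling, randomise within those groups. The section should say what information the screening uses, since the callers' file has no survey data.

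The work is sorting each contact sheet by a random number. The downside is a short delay for the first volunteers in each batch while the batch is assembled. No extra interviews or change to the target of 215 are needed, and nothing is lost if the pool proves small enough that everyone is called.

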### Study design overview

This mixed-methods study will involve two stages. Stage One will undertake an Australia-wide audit of a representative sample of RUM bins. The objectives of this stage are:To quantitatively describe the amount and types of medicines returned to pharmacies using a statistically valid sample of returned RUM bins from all states and territories of Australia; andTo identify the proportion of waste that is PBS-subsidised and to extrapolate the value of ‘wastage’ to the PBS.

In Stage Two a two-step general population survey will be conducted. Step One will utilise an online household survey with a general population sample. Step Two will invite a sub-set of survey respondents from Step One who take five or more medicines, to participate in a telephone interview. The objectives of Stage Two are:To assess general population awareness of: the NatRUM scheme; practices for the disposal of unwanted medicines; and the risks of accumulating medicines;To identify general population practices for household disposal of unwanted medicines in the previous 12 months;To quantitatively describe the volume of unwanted or expired medicines stored in the households of a sub-set of the general population with higher medication burden; andTo qualitatively explore the storage and disposal practices of a sub-set of the general population with higher medication burden.

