If time permits, and the participant agrees, they will be asked their views on what they think happens to medicines returned to pharmacies, if they have any concerns or issues with returning medicines, and the perceived risks of keeping unwanted medicines at home. Lastly, demographic information will be collected.

Interviews also present opportunities for the pharmacist researchers to provide information about discarding medicines via the participant’s local pharmacy.

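### The interview sub-sample of people taking five or more medicines is benchmarked to the all-adult census, and the article describes no source of age, gender or state for screening before the interview

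*Protocol article*

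**What the plan says.** Stage two, Step two recruits "a sub-sample of the survey respondents who self-identify as taking five or more medicines". One Stage Two objective (Study design overview) is to describe quantitatively the unwanted or expired medicines "stored in the households of a sub-set of the general population with higher medication burden".

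On numbers, Step two, Participants states: "We propose to interview around 5% of the survey sample (i.e. 215 participants". Eligible volunteers are contacted sequentially. The section adds, conditionally, that purposive screening may be called for "to achieve a national representative sub-sample based on gender, age and geographical location from the 2011 census data". The Limitations section then lists purposive screening among the strategies against selection bias.

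The same census source is the benchmark for the whole adult survey, where the panel company seeks a "national representative sample based on gender, age and geographical location from the most recent census (2011) data" (Step one, Participants, with Table 3).

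On data flow, the researchers receive a separate "spreadsheet containing contact information only (i.e. not including any survey response data". Age, gender and state are survey questions (Step one, Survey and data collection), and the survey file arrives de-identified (Step one, Data analysis). In the interview, after the medicine questions, "Lastly, demographic information will be collected" (Step two, Interview guide and data collection).

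**The concern.** A benchmark should describe the population that the results are about. The volume objective is about adults with a higher medication burden, whereas census margins describe all adults. The two coincide on age, gender and place only if taking five or more medicines is unrelated to all three, and the article does not claim that. Moving the interviews towards census margins would then give too much weight to the kinds of people who seldom take five or more medicines. A step listed as protection against selection bias could add bias, and the result could be reported as nationally representative.

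A second tension concerns how the screening would work. Nothing described tells the interviewer a respondent's age, gender or state before the interview. As described, interviewers learn these only after most of the effort has been spent.

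At stake is mainly the descriptive estimate of stored volume. The thematic analysis depends much less on the demographic mix.

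**Working it through.** **Inputs from the article**
- Survey size: "A sample size of 4300 is proposed for our general population survey". The Table 3 header prints 4302.
- Interview target: 215, given as 5% of the survey sample.
- Table 3 age shares: 12, 18, 19, 18, 15 and 18% for ages 18–24, 25–34, 35–44, 45–54, 55–64 and 65–99.
- Table 3 survey targets: 516 aged 18–24 and 774 aged 25–34.

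**The plan's own figure.** 0.05 × 4300 = 215.0, and 0.05 × 4302 = 215.1. The stated 215 reproduces.

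**What full census balance would mean.** Share × 215 gives 25.8, 38.7, 40.9, 38.7, 32.3 and 38.7. So about 39 interviews (18%) fall at 65 or over, and 0.30 × 215 = 64.5 at ages 18–34. The article sets no interview quotas. These counts only apply its benchmark to its target.

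**What a matching sample might hold.** The article gives no age mix for people taking five or more medicines, so the share *s* aged 65 or over is an assumption, varied from 30% to 60%. To illustrate bias, assume also that mean stored volume at 65 or over is 1.5 times the mean below 65.
- Matching count = 215 × *s*.
- Relative error of an unweighted, census-balanced mean = (0.18 × 1.5 + 0.82) / (1.5*s* + 1 − *s*) − 1 = 1.09 / (1 + 0.5*s*) − 1.
- Effective size if such a sample is weighted back on two age groups with equal variances = 215 / [*s*²/0.18 + (1 − *s*)²/0.82].

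| Assumed *s* | Matching count at 65+ | Error of mean | Effective size |
|---|---|---|---|
| 30% | 64.5 | 1.09/1.15 − 1 = −5.2% | 215/1.098 = 196 |
| 40% | 86.0 | 1.09/1.20 − 1 = −9.2% | 215/1.328 = 162 |
| 50% | 107.5 | 1.09/1.25 − 1 = −12.8% | 215/1.694 = 127 |
| 60% | 129.0 | 1.09/1.30 − 1 = −16.2% | 215/2.195 = 98 |

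The error from age is zero if *s* = 18%, or if volume does not differ by age.

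**Whether census balance could be reached.** If 2% of those aged 18–24 and 3% of those aged 25–34 took five or more medicines (assumption), the survey would hold 516 × 0.02 + 774 × 0.03 = 10.3 + 23.2, or about 33 eligible people, for 64.5 places. Full balance would then be out of reach.

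**Data flow, side by side**
- Contact sheet: no survey answers, so none of the survey's age, gender or state items.
- Survey file: de-identified, with no linking identifier described.
- Interview: demographics come at the end.

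None of the three, as described, supports screening before the interview.

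**The case against.** Several stronger readings are tempting, and the article does not support them.

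- **A reader might infer that the sub-sample will be forced to census margins.** Sequential contact is the default, screening is conditional, and no interview quotas are set. What stands is that the census is the only benchmark named, and Limitations counts the screening as a safeguard.
- **A reader might infer that screening is impossible.** The article does not exclude a short question at the start of the call, or release of contacts in batches by the panel company, which already manages demographic targets for the survey. It also refers to a separate interview protocol that is not shown. What stands is a tension in the data flow described.
- **A reader might combine both harms in full.** They limit each other: if screening cannot be done, or young eligible respondents run out, the sample cannot be pulled all the way to census margins.
- **A reader might infer that non-response cannot be checked.** If the screening answer is kept in the survey file, eligible respondents can be compared with interviewees in aggregate. Only a person-level comparison of people not reached lacks a described route.
- **A reader might state a fixed degree of under-sampling of older people.** Any such figure needs an outside age mix. The definition also counts complementary, alternative and over-the-counter medicines, which makes the group broad.

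It is also fair to say that Step Two is descriptive and thematic, that interviewing may stop at saturation before 215, and that Limitations already discloses self-selection and non-contact. Those disclosures do not address the choice of benchmark.

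**Conclusion.** The point holds in a limited form. The article names an all-adult benchmark for a sub-sample defined by taking five or more medicines. That does not fit its own volume objective and should be changed. Bias follows only if the screening is applied and if both eligibility and stored volume vary with age, gender or place.

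The size is unknown from the document. Under the assumed 30% to 60% aged 65 or over, full census balance would supply 39 such interviews where a matching sample has about 65 to 129. With the further assumed volume ratio of 1.5, the unweighted mean would be about 5% to 16% too low. These are illustrations, not estimates.

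The data-flow limb is an unresolved tension between the described steps. It does not show that screening cannot be done.

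**What to change.** **Benchmark.** In Step two, Participants, replace the 2011 census with the gender, age and state distribution of Step One respondents who report five or more medicines. The screening question closes the main survey, so the study can supply this distribution itself, provided the answer is kept in the survey file. Alternatively, leave recruitment sequential and weight the interview volume results to that distribution, using the demographics the interview already collects. Reword the Limitations sentence to match.

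**Screening, if used.** State how it is done before the call. Either the panel company releases contacts by cell, or it adds age band, gender, state and a study ID to the contact sheet, subject to ethics approval, because survey answers would then travel with telephone numbers.

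**Cost.** A changed reference distribution costs almost nothing before interviewing starts. The data transfer changes slightly. Weighting loses some precision: in the illustration, weighting back a fully census-balanced sample would leave 215 interviews worth about 196 to 98. Setting the right benchmark at recruitment avoids most of that loss. The new benchmark still carries the panel's own selection, which the article already acknowledges.
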